### Study design

This trial is a prospective multi-center, single-blind two-arm RCT comparing mild versus moderate hypothermia for circulatory arrest in hemiarch surgery on a composite outcome of neurological and acute kidney injury (AKI) in 282 patients undergoing aortic hemiarch surgery with uSACP. Consenting adult patients (≥ 18 years of age) undergoing ascending aorta and hemi-arch replacement with uSACP and an anticipated circulatory arrest time of less than 20 min will be randomized 1:1 to moderate hypothermia (26 ± 1 °C, Control group) versus mild hypothermia (32 ± 1 °C, Treatment group).

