#### Transfusion strategy

Transfusion triggers (for packed red blood cells only) will be adhered to whenever possible without compromising patient safety or center-specific transfusion protocols. Thus, a liberal transfusion threshold of Hb < 95 g/L will be used intraoperatively and in the intensive care unit (ICU), while a Hb < 85 g/L will be adhered to after transfer to the ward. These values were chosen based on the TRICS-III trial (Transfusion requirements in Cardiac Surgery III) and will be used for the duration of the patients hospital stay [25].

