i.Delirium assessment will be performed using CAM
For a diagnosis of delirium by CAM, the patient must display:
Presence of acute onset and fluctuating course ANDInattentionAnd either one of:
Disorganized thinking ORAltered level of consciousnessii.Assessments will be performed on POD 2 ± 2 and 6 **±** 14.Death
All cause postoperative 60-day or in-hospital mortality5.Cardiopulmonary bypass (CPB) time (minutes)6.Bleeding rates to qualify for mediastinal re-exploration
Indication for exploration defined as postoperative mediastinal bleeding of [40, 41]:
i.500 ml in any one hourii.1000 ml in any 4-h periodiii.Or at surgeons discretion7.Incidence and quantity (number of units/patient) of perioperative blood transfusions
Defined as all intraoperative and postoperative transfusions up to POD 7 or discharge (whichever comes first)The transfusion of packed red blood cells (pRBCs) will adhere to the previously defined transfusion trigger strategy whenever possible without compromising patient safety
i.A liberal transfusion threshold of Hb < 95 g/L will be used intraoperatively and in the ICU, while a Hb < 85 g/L will be adhered to after transfer to the wardNumber of platelets, fresh frozen plasma (FFP), and cryoprecipitate will also be tabulated for the same time period
i.No transfusion triggers given and left to discretion of caring physician8.Prolonged mechanical ventilation
Defined as those requiring ≥ 48 h of mechanical ventilationMeasured in hours from time of admission to the ICU9.Perioperative myocardial infarction
Clinically diagnosed using a combination of electrocardiographic (new Q wave on 12 lead ECG) and biochemical (troponin I > 45 ng/L) markers or both10.Length of stay
ICU hoursHospital days11.Quality of life (SF-12) survey
A measure of perceived health (health-related quality of life) that describes the degree of general physical health status and mental health distress [42]Will be assessed preoperatively and on POD 60 ± 14

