### Blinding, clinical/study staff, and participant confidentiality

Knowledge of the patient’s treatment arm has the potential to bias postoperative care, especially with respect to transfusion strategies and decision-making when seeking neurodiagnostic imaging for possible deficits. In order to limit these biases, patient temperatures and CPB times will be redacted from the relevant operative room (OR) records shortly after surgery. This will be performed by a dedicated un-blinded assistant at all study sites. Operating surgeons will also be instructed not to include CPB time or patient temperatures in their dictated operative notes. A copy of the un-redacted OR records will be placed in a sealed envelope and placed with the patient’s chart. The envelope will have the name and contact information of the principal investigator (PI), with instructions to open the envelope only if there is a medical need to know the patients intraoperative temperature or CPB time.

It will be suggested that clinical staff speak directly with the PI prior to opening this envelope. Upon the patient’s discharge, the envelopes will be stored in a locked file cabinet in the Clinical Research Office. As the envelopes contain identifiable information, they will not be stored with the patient’s study file.

As the administration and/or scoring of both the neurocognitive tests and the quality of life questionnaire may be prone to bias, any study staff administering neurocognitive tests and quality of life questionnaires will be blinded to the patient’s group assignment at all times.

All study-related information, including case report forms (CRFs), evaluation forms, and consultation reports, will be kept strictly confidential. All records will be kept in a secure, locked location and only research staff will have access to the records. Subjects will be identified only by means of a study ID number specific to each subject. All computerized databases will identify subjects only by study ID numbers and will be maintained on secure hospital servers.

A password-protected master list containing both the study ID and the patient’s name and contact information will be maintained on a secure hospital server, in a folder accessible only by study staff.

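### The re-exploration endpoint can be met on surgeon discretion, very probably with the arm known, and the transfusion endpoint pools units given before and after the records are masked

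*Protocol article*

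**What the plan says.** All references are to the protocol article.

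**Re-exploration** (Secondary outcomes and definitions, item 6). The endpoint is headed "Bleeding rates to qualify for mediastinal re-exploration". The definition begins "Indication for exploration defined as postoperative mediastinal bleeding of", lists 500 ml in any one hour and 1000 ml in any 4-hour period, and closes with "Or at surgeons discretion".

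**Transfusion** (same section, item 7). The endpoint is the incidence and number of units per patient: "Defined as all intraoperative and postoperative transfusions up to POD 7 or discharge (whichever comes first". For platelets, fresh frozen plasma and cryoprecipitate the text says "No transfusion triggers given and left to discretion of caring physician". For red cells, Transfusion strategy sets haemoglobin thresholds common to both arms (95 g/L in theatre and the ICU, 85 g/L on the ward), with a qualification: "Transfusion triggers (for packed red blood cells only) will be adhered to whenever possible without compromising patient safety or center-specific transfusion protocols".

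**Masking.** Study design states: "This trial is a prospective multi-center, single-blind two-arm RCT". The section on blinding says that knowledge of the arm "has the potential to bias postoperative care, especially with respect to transfusion strategies". Its remedy is to redact temperatures and bypass times from the operating records soon after surgery, and to tell operating surgeons to leave both out of their dictated notes.

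**Data collected** (Frequency and duration of follow-up). Intraoperative red cell units are an item of their own. Chest tube outputs are listed separately from re-exploration for bleeding or tamponade.

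**The concern.** An endpoint named as a bleeding rate should respond to bleeding. Item 6 also responds to a decision, and the person deciding very probably knows the allocation. Item 7 has a related weakness. The protocol itself names transfusion as prone to bias from knowledge of the arm and takes a step against it, but that step begins only after the operation. Units given earlier enter the same total.

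The direction of any bias can be guessed, though not established. The Background cites less coagulopathy under mild hypothermia in case studies, and pilot data from the principal site showing lower need for blood products than under deep hypothermia. A clinician who shares that expectation could re-explore, or give untriggered products, somewhat sooner in the colder arm. Bleeding and transfusion would then appear to favour mild hypothermia without any difference in blood loss. The Abstract lists both among the secondary outcomes and says the results will be used to write guidelines.

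**Working it through.** No figure in the protocol sizes this point, so the check is mainly of the text. A conditional illustration follows.

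**1. Does the surgeon know the arm?** The article does not say so directly, and item 6 does not say that the surgeon concerned is the one who operated. Three facts point that way:
- The trial is single-blind.
- The operation is carried out at the assigned temperature.
- Operating surgeons are told not to dictate temperatures, which presumes that they know them.

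The only staff said to be blinded at all times are those who give the neurocognitive tests and quality of life questionnaires. The inference is strong, but it remains an inference.

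**2. Is the discretionary route needed to measure bleeding?** No. The first two criteria are volumes, and chest tube output is collected. The article does not give the recording interval, and the criteria need hourly values.

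**3. Which transfusions are exposed?**

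| Product | Trigger | Intraoperative count listed separately |
|---|---|---|
| Red cells | Common haemoglobin threshold, used where possible | Yes |
| Platelets, plasma, cryoprecipitate | None | Not shown |

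Intraoperative units of every product precede redaction. The second row carries most of the exposure.

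**4. Is the sample size touched?** No. It rests on the composite, 35% versus 20%. With unpooled variance, two-sided 5% and 80% power: n = (1.960 + 0.842)² × (0.35 × 0.65 + 0.20 × 0.80) / 0.15² = 135.2 per arm. Multiplied by 1.05 this is 141.9, close to the stated 141. Neither endpoint 6 nor endpoint 7 enters the calculation.

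**5. Illustration, with assumed rates.** Take n = 141 per arm, no true difference, a base rate p in both arms, and discretionary calls that add s to one arm, so that p₁ = p + s and p₂ = p. Let p̄ be the mean of p₁ and p₂. The chance of p < 0.05 is

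Φ((s − c)/SE₁) + Φ((−s − c)/SE₁),

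with c = 1.96 × √(2p̄(1 − p̄)/n) and SE₁ = √((p₁(1 − p₁) + p₂(1 − p₂))/n).

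Example with p = 5%, s = 2 points: c = 1.96 × √(2 × 0.06 × 0.94/141) = 0.0554 and SE₁ = √((0.0651 + 0.0475)/141) = 0.0283. The result is Φ(−1.25) + Φ(−2.67) = 0.109.

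| Base rate | s = 0 | s = 2 points | s = 3 points | s = 5 points |
|---|---|---|---|---|
| 3% | 5.0% | 13.7% | 22.8% | 45.3% |
| 5% | 5.0% | 10.9% | 17.5% | 35.7% |
| 8% | 5.0% | 9.0% | 13.8% | 27.7% |
| 10% | 5.0% | 8.3% | 12.4% | 24.5% |

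A modest shift would usually not reach significance. An observed 8% versus 11% gives z = 0.03 / √(2 × 0.095 × 0.905/141) = 0.86, p about 0.39.

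**The case against.** The case on the other side is substantial, and much of it stands.

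- **Discretion has a function.** The follow-up section counts re-exploration for tamponade, which a volume rule can miss, and item 6 is worded as a clinical indication. This stands. It argues for reporting all re-explorations as an outcome of their own, but not for merging them with a bleeding rate.
- **Red cells have a safeguard.** The threshold is the same in both arms and applies in theatre. A reader might infer that all intraoperative units are equally exposed; the trigger means that they are not, although it is qualified.
- **The periods can partly be separated.** A reader might infer that open and masked transfusions are inseparable. For red cells the intraoperative count is collected. For the other products the article shows no split, though the full protocol may have one.
- **Pooling is defensible.** Products given in theatre alter later need, so total perioperative use is a sensible quantity. For the same reason it would be wrong to require that the two periods agree before a transfusion effect is believed.
- **The postoperative period is not cleanly blinded.** Redaction is meant to limit bias, is not stated to be complete on ICU arrival, and the sealed envelope may be opened for medical need. A contrast of open with blinded care would claim too much.
- **Open care in theatre is unavoidable, and splits by period are often left to the SAP.** Both are true. But the discretionary route and the pooled window are definitions that the article fixes, not details that it leaves out.

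**Conclusion.** The point holds in a limited form. Item 6 admits a route that needs no measured bleeding and is very probably taken with the arm known. Item 7 combines units given before the masking step with units given after it, and the exposure is mainly in the three products without a trigger. These are two of eleven secondary endpoints, and the primary composite and the 282-patient sample size are unaffected.

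The size of the bias cannot be derived from the documents, and the rates in the illustration are assumptions. A reader might go further and infer that a spurious advantage for mild hypothermia is likely, or that less bleeding is the trial's main expected benefit. The documents support neither. The stated hypothesis concerns neurologic injury and AKI, and the pilot comparison was with deep, not moderate, hypothermia. Nor did the surgeon choose the temperature; it is randomized.

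The change is still worth making, because it is nearly free and removes an avoidable source of doubt about two outcomes on which the investigators hold a published expectation.

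**What to change.** Leave clinical practice as it is and change only how the outcomes are counted.

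1. **Bleeding.** Define the endpoint as either volume criterion met, from recorded chest tube output. Ask sites to confirm that output is recorded hourly. Report re-exploration for any reason, including tamponade, as a separate outcome, with the number done on discretion alone.
2. **Transfusion.** Keep total perioperative transfusion as the endpoint. Also report it by period (intraoperative, postoperative) and by product. State beside the table that intraoperative decisions are open-label and that postoperative masking is only partial. Do not make any conclusion depend on agreement between the periods.

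The cost is a change to definitions, a few more outcome rows, and recording platelets, plasma and cryoprecipitate by period where this is not already done. Intraoperative red cell units and chest tube output are already on the collection list.

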### Statistical consideration

In a prospective contemporary study of patients over the age of 65 years undergoing aortic valve replacement, Floyd and colleagues observed an incidence of clinical stroke of 17% using similar assessment modalities to those proposed in this trial [26]. Interestingly, clinically documented strokes in the Society of Thoracic Surgeons (STS) adult cardiac surgery database in the same patients were only 7%, suggesting that careful and systematic documentation can reveal a ~ 2.5-fold higher incidence of neurologic injury than routine clinical evaluation. Furthermore, this study found increasing CPB to be an important risk factor for neurologic injury [26].

In patients undergoing aortic arch surgery, the incidence of neurologic injury is expected to be higher due to a variety of reasons, including longer CPB times, manipulation of the aortic arch and branch vessels for cannulation or clamping, and injury associated with hypothermia and re-warming. In a large retrospective study of over 45,000 patients undergoing proximal aortic arch replacement surgery, Williams et al. found a clinical stroke rate of ~ 6.62%.[43] Notably, the authors did not include patients who may have suffered TIAs or other temporary neurologic dysfunction. Their data were also obtained from the STS database, with no prospective or systematic neurologic evaluation. Thus, for the purpose of this RCT, we hypothesize that patients in the moderate hypothermia group will experience a 15–20% incidence of neurologic injury.

With respect to the incidence of AKI, previously reported rates of stage 1 AKI in patients undergoing cardiac surgery by Boodhwani and colleagues have revealed an incidence of around 22.35% based on the Acute Kidney Injury Network (AKIN) criteria for staging AKI [44]. Their study population was a mixed surgical population with infrequent procedures such as heart transplantation, ventricular assist device placement, and complex congenital abnormality repair being excluded.

This RCT will use the newer KDIGO criteria for assessing AKI, which identifies significantly more AKI in patients than both the Risk, Injury, Failure, Loss of kidney function, and End-stage kidney disease (RIFLE) and AKIN criteria [38, 45]. Specifically, KDIGO criteria have been shown to have a greater sensitivity in diagnosing AKI when compared to RIFLE and AKIN (51% versus 46.9% for RIFLE, *p* <  0.01 and 38.4% for AKIN, *p* <  0.001) [45]. It is also expected that the incidence of AKI will be higher in this study based on the type of surgery being performed, which necessitates a period of lower body ischemia time. Thus, we hypothesize a 25% incidence of KDIGO stage 1 AKI for this trial.

#### Sample size

Taking into consideration the aforementioned incidence rates of both neurologic injury and AKI, a composite outcome of ~ 35% should represent the incidence of these injuries in patients undergoing hemiarch surgery using traditional methods of hypothermia. This accounts for a 5–10% overlap that will likely exist, where a patient will suffer both types of injuries.

We hypothesize that circulatory arrest using mild hypothermia (32 °C) and uSACP during aortic hemiarch surgery will result in a 15% absolute risk reduction in composite outcomes (neurologic injury and AKI) from 35% to 20%. With an alpha (type 1 error) of 0.05 and power of 80%, and a 5% loss to follow-up, approximately 141 subjects will be needed in each group for a total of a 282 patients.

#### Clinical significance

As mentioned, strokes post-cardiac surgery have been shown to double the duration and costs of hospitalization, and are associated with increased mortality and severe physical disability [12]. Similarly, kidney injury resulting in end-stage renal disease is a major health problem due to its high morbidity and mortality, as well as having social and financial implications [46]. These post-operative complications result in significant lifestyle morbidity, as well as added expenditures to the health care system.

With an absolute risk reduction (ARR) of 15%, the relative risk (RR) and RR reduction (RRR) would be 57% and 43%, respectively, suggesting the proposed intervention carries benefit, and has a medium-sized “relative” effect, with only seven patients needing to be treated with the mild hypothermic strategy to avoid an adverse event. Considering the proposed intervention adds no extra costs, with temperature being the only variable manipulated in the normal standard of care for these patients, the proposed intervention potentially carries both a significant and meaningful benefit to patients while reducing health care expenditure.

#### Statistical analysis

The trial will be analyzed on a true intention to treat (ITT) basis, including all trial participants who were randomized regardless of adherence to treatment protocol, including those who are lost to follow-up or may have died. Patient crossover will be tracked and reported with the final trial results. In addition, a ‘modified ITT’ analysis will be performed (excluding patients not assessed for the primary outcome or lost to follow-up and/or early death) to account for potential biases introduced with ITT analyses.

The primary endpoint of our composite outcome will be evaluated using a chi squared test (or Fisher’s exact test if cell count is < 5 in any cell). Categorical secondary endpoints will be analyzed in the same method, while continuous secondary endpoints will be analyzed using Students *t*-test (or Wilcoxon rank sum test if the data are not normally distributed). Continuous variables will be reported as mean ± standard deviation or median (interquartile range [IQR]) for non-normally distributed variables. Categorical variables will be reported as counts and percentages. As the primary outcome is a composite of both neurologic and AKI, secondary outcome analysis will pay particular attention to individual assessment of these indices for treatment effect and positive correlation.

Exploratory multivariable logistic regression analysis will be performed to determine risk factors for neurologic and renal complications post-operatively. A *p* value of < 0.05 will be considered statistically significant. Multivariable analysis will include variables with *p* <  0.20 in univariate analysis in addition to clinically significant variables.

Once data collection is complete for all study participants, a statistical analysis plan (SAP) will be created prior to data analysis and release of results. As the principle statistician involved in this trial, [name] (PhD) will primarily be responsible for this analysis. [name] is the Director of the Cardiovascular Research Methods Centre at the UOHI and Professor in the School of Epidemiology, Public Health and Preventive Medicine at the University of Ottawa.

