#### Postoperative assessment and follow-up study visits

On postoperative days 2 ± 2 days, 6 ± 1 days, and 60 ± 14 patients, will undergo neurocognitive screening by trained personnel. NIHSS and MOCA examinations will be made at each time point (or prior to discharge for time point 6 ± 1 days). In the event a neurological deficit is identified during assessment and/or based on patient symptoms (focal/global, motor/sensory loss, or prolonged delirium/agitation), neurological imaging will be obtained using computed tomography (CT) head or diffusion-weight magnetic resonance imaging (DW-MRI). MRIs will be used only if symptom onset is acute in nature requiring rapid diagnosis. Patients will also undergo MRS assessment only in the event of a postoperative stroke. BI scoring will be performed preoperatively and postoperatively only in the event of a stroke. Quality of life measures will be assessed using SF-12 health survey and obtained preoperatively and at final follow-up at 60 ± 14 days (see SPIRIT Fig. 1).

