#### Primary outcome and definitions

The primary efficacy endpoint for this study will be a composite of neurologic injury and AKI that occurs at any time over the 60 ± 14 day study period. Definitions are defined in secondary outcomes below.

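### The supplementary modified ITT drops early deaths and losses to follow-up even when a primary event is already recorded, so it cannot serve as a correction for ITT bias

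*Protocol article*

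**What the plan says.** The Statistical analysis section makes true ITT the main analysis, "including all trial participants who were randomized regardless of adherence to treatment protocol, including those who are lost to follow-up or may have died". It then adds a modified ITT, "excluding patients not assessed for the primary outcome or lost to follow-up and/or early death", and gives its purpose as "to account for potential biases introduced with ITT analyses". Early is not defined. Nothing is said about a patient who meets an exclusion ground after a primary event has been recorded.

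The primary endpoint is "a composite of neurologic injury and AKI that occurs at any time over the 60 ± 14 day study period". Death is not a component. It is a separate secondary endpoint, "All cause postoperative 60-day or in-hospital mortality".

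Ascertainment starts early. Under Secondary outcomes and definitions, creatinine is taken on postoperative days 0, 1, 2 ± 2, 4 ± 1, 6 ± 1 and 60 ± 14. Neurologic screening follows a similar calendar: "On postoperative days 2 ± 2 days, 6 ± 1 days, and 60 ± 14 patients, will undergo neurocognitive screening by trained personnel".

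**The concern.** Loss to follow-up and early death stand in the rule as grounds of their own, alongside not having been assessed. A patient with a stroke on day 1 who dies on day 4, or with AKI on day 2 who misses the day-60 visit, has a known primary outcome and is still removed. The analysis set then depends on death and loss, both of which occur after randomization and may depend on treatment.

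At stake is the only alternative population that the article names for the primary endpoint. Readers will use it to judge how robust the main result is. If those removed carry more events than the rest of their arm, and more are removed from one arm, that arm looks better than it was. The stated purpose makes this worse, because it invites readers to trust the modified set over the ITT result where the two differ.

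**Working it through.** **Inputs from the protocol article.** 141 patients per arm (Sample size); chi-squared test on proportions (Statistical analysis); endpoint window and visit calendar as above. The plan gives no figure for the modified set, so there is none to reproduce. The 141 serves only as a denominator.

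**Assumed inputs.** Event counts, early deaths by arm, and how many of the dead had a prior event. None of these is in the documents, so a range is shown.

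**Effect on one arm.** With N patients and E events, removing d patients of whom k had an event changes the rate by

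(E − k)/(N − d) − E/N = (E·d − k·N) / (N·(N − d)).

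The rate falls only if k/d exceeds E/N, that is, only if those removed are enriched for events.

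**Main illustration.** Control: E=44, d=2, k=1. Mild hypothermia: E=30, d=6, k=5.

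- Control: (44×2 − 1×141)/(141×139) = −53/19,599 = −0.3 points.
- Mild: (30×6 − 5×141)/(141×135) = −525/19,035 = −2.8 points.
- Net shift in favour of mild: about 2.5 points.

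**Test.** Pooled z-test, equivalent to the uncorrected chi-squared test. ITT: pooled rate 74/282 = 0.2624, SE = √(0.2624 × 0.7376 × 2/141) = 0.0524, z = 0.0993/0.0524 = 1.895, p=0.058. Modified ITT: 43/139 vs 25/135, z = 2.38, p=0.017.

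| Case (assumed counts) | Control | Mild | Difference, points | p |
|---|---|---|---|---|
| ITT | 44/141 (31.2%) | 30/141 (21.3%) | -9.9 | 0.058 |
| Modified ITT as written; 2 vs 6 deaths, 1 and 5 with events | 43/139 (30.9%) | 25/135 (18.5%) | -12.4 | 0.017 |
| Same deaths, 1 and 2 with events | 43/139 (30.9%) | 28/135 (20.7%) | -10.2 | 0.054 |
| First death scenario, documented events kept | 44/140 (31.4%) | 30/140 (21.4%) | -10.0 | 0.058 |

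**Other starting points, with the first death scenario (1 and 5 with events).**

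- No effect (44/141 in each arm): the modified ITT gives 43/139 vs 39/135, 30.9% vs 28.9%, a false difference of -2.0 points, p=0.71.
- Harm from mild hypothermia (30 vs 44 events): the modified ITT gives 29/139 vs 39/135, 20.9% vs 28.9%. The excess shrinks from 9.9 to 8.0 points but does not reverse.

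**A larger imbalance.** With 49/141 events in each arm and 3 vs 10 deaths (2 and 8 with events), the rule as written gives 47/138 vs 41/131, a false difference of -2.8 points. With documented events kept, it is 49/140 vs 49/139, or +0.3 points.

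**Loss to follow-up.** 5% of 141 is about 7 per arm. Starting from 49/141 in each arm, if the 7 lost include 2 known events in control and 5 in mild, the rule gives 47/134 vs 44/134, or -2.2 points. If losses carry events at each arm's own rate, neither rate moves.

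**Is enrichment plausible?** The Background section cites a five- to tenfold increase in early mortality with stroke after cardiac surgery. Applied to the 15–20% neurologic injury assumed for the moderate arm, the share of early deaths with a prior neurologic event would run from 0.15×5/(0.15×5 + 0.85) = 47% to 0.20×10/(0.20×10 + 0.80) = 71%, against a planned composite rate of 35%. This is rough, because the 15–20% includes TIA, but it makes enrichment more than a theoretical possibility.

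**The case against.** The strongest reply is that the modified ITT is only an addition. The main analysis keeps everyone randomized, "including those who are lost to follow-up or may have died". Mortality is reported separately, and a data safety monitoring board meets twice a year, so an excess of deaths would be seen. The article gives the modified set no role in the trial's conclusion. All of this stands, and it limits the severity.

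A second reply is that death and loss may be meant only as reasons why the outcome is unavailable, which would make this a complete-case set. That is possible, but the wording joins them as alternatives and does not say so. One sentence would settle it.

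A third reply is that the move across 0.05 reflects a starting p of 0.058. That is correct. The substantive result is a shift of 2 to 3 points, and only under enrichment.

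Stronger readings are tempting, and the document does not support them:

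- A reader might infer that the ITT table counts a death without stroke or AKI as a success. The article gives no scoring rule for such patients, and that may properly be left to the analysis plan.
- A reader might infer that the ITT also understates severe stroke. It does not: stroke is a component of the endpoint and counts whenever it occurs in the window.
- A reader might see a conflict with the sample size, which allows for loss ("and a 5% loss to follow-up, approximately 141 subjects will be needed in each group"). Enlarging the sample for loss while keeping all randomized patients in the ITT set is ordinary practice.

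**Conclusion.** The point holds in a limited form. As written, the modified ITT discards documented primary events and selects on post-randomization outcomes, so it is not a correction for bias in the ITT analysis. It can flatter the arm with more early deaths, provided that deaths differ between arms and the dead are enriched for events. Under the assumed 2 vs 6 deaths, the shift is about 2.5 points with 5 of 6 enriched and about 0.3 points with 2 of 6.

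A reader might go further and conclude that the rule would turn harm into apparent benefit. The figures do not show that: starting from harm, the same exclusions reduce the excess from 9.9 to 8.0 points and leave its direction unchanged.

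Every death count and prior-event share here is an assumption. This should be fixed, but it does not threaten the main analysis.

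**What to change.** In the modified ITT:

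- keep every randomized patient with a documented stroke, TIA or AKI, whatever happens later;
- exclude only event-free patients whose outcome assessment is incomplete;
- replace the stated purpose with a plain description: a sensitivity analysis for missing outcomes.

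Optionally, add one sensitivity analysis in which death before any component counts as an event.

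The cost is a few lines of wording and, with the option, one extra run. No new data are needed. The revised set is still not neutral, because dropping only event-free patients raises the rate slightly in the arm that loses more of them. With 2 vs 6 deaths, 1 and 2 with events, it gives 44/140 vs 30/137, or -9.5 points against -9.9 in the ITT. That is why it should be labelled a sensitivity analysis. The article says the analysis plan will be written after data collection is complete, so the wording should be settled before anyone sees results by arm.
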